### Sample Size

The study includes 13 patients; 10 patients are expected to be sufficient to perform a feasibility study and gather information on the potential of unsupervised therapy to plan a subsequent larger study targeting efficacy, and a dropout rate of around 20% is accounted for based on our previous studies [26]. The selected sample size guarantees the execution of the study within a relatively short time (ie, 2 years) such that improvements to the device, if needed, can be implemented in a timely manner for follow-up studies. Furthermore, this sample size is comparable to previous studies performed by our group with the RHK and to other studies with similar goals [10,11,15].

### Data Collection, Management, and Confidentiality

All the data listed herein are collected by trained personnel. For withdrawn participants, the clinical and robotic data collected until withdrawal are kept, and no further clinical or robotic evaluations are performed after that. A specific follow-up phase is not needed.

At the beginning of the study an ID is assigned to each patient and the saved data are coded according to this ID. Study data are reported on a paper case report form (CRF), 1 for each patient, and then entered in an electronic CRF with the help of an electronic database, namely Research Electronic Data Capture (REDCap) [38,39], hosted on a secure server at the Swiss Federal Institute of Technology Zürich. REDCap promotes data quality via functions and settings, like audit trails, field type restriction, range checking, and definitions of required fields. Data automatically saved by the RHK are stored on the connected laptop. Backups of the data saved on the laptop and of the electronic CRF are saved monthly on the protected server of the sponsor institution. To promote security, the laptop is password protected and participants can only access the therapy interface. The data will be archived for a minimum of 10 years after study termination or premature termination of the clinical trial.

### Data Analysis

Descriptive statistics will be used to describe the study population (eg, demographics, initial clinical scores, and changes in clinical scores, such as functional recovery), attendance and therapy dose in the unsupervised phase, user experience, and platform usability.

Normal distribution of the data will be checked with the Shapiro Wilk test. For each usability metric, a paired *t* test (normal distribution) or a paired samples Wilcoxon test (for data not normally distributed) will be performed to compare the data collected during the usability evaluation 1 and usability evaluation 2 sessions.

To evaluate the content of unsupervised therapy, 1-way repeated measures ANOVA or its nonparametric version (Friedman test) with post hoc tests will be run to compare intensity (average block intensity for each patient), performance, and ratio of effective therapy time to total session duration during supervised, minimally supervised, and unsupervised therapy. The same tests will be used to compare the answers to the VAS-smiles, a 5-point VAS represented by different emoticons, performed at the end of each therapy session during the 3 phases. For these comparisons, we expect therapy content and VAS-smiles not to vary significantly depending on the level of supervision, as ideally the absence of the therapist should not impact these outcomes. Patients who did not reach the unsupervised phase will be excluded from this analysis.

Linear mixed-effects models will be used to investigate parameters (eg, demographics and baseline data) possibly influencing the achieved dose of unsupervised therapy.

Relevant qualitative data will be summarized and reported accordingly.

Data analysis will be performed with MATLAB R2021b (MathWorks).

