**Figure 2 figure2:**
[figure not shown]
Design of the interventional study for each of the study participants. All participants undergo a screening visit, baseline assessments, 1 week of supervised therapy, and 1 week of minimally supervised therapy. After the first week of minimally supervised therapy, the therapist checks whether the patient properly learned how to use the technology and is ready for unsupervised training. If yes, the patient proceeds to 2 weeks of unsupervised use. If no, an additional week of minimally supervised therapy is performed. At the end of this second week, the therapist checks again whether the patient can train independently. If yes, the patient proceeds to 1 week of unsupervised therapy. If no, an additional week of minimally supervised therapy is performed. In total, each patient performs 4 weeks of technology-assisted rehabilitation. At the end of the protocol, the clinical and robotic assessments as well as the evaluation of the user experience and usability are repeated for all patients.

**Table 1 table1:** Data collected and procedures (marked with an “X”) performed at each time point of the clinical trial, with primary (PO) and secondary (SO) outcomes indicated. Day 0 corresponds to the first supervised robot-assisted therapy session. The time range indicates how far a procedure can be advanced (–) or postponed (+) for organizational reasons from the precise time point at which it should be performed.

		Screening visit	Baseline clinical assessment	Baseline robotic assessment	Robot-assisted therapy sessions		Usability evaluation 1	Robot-assisted therapy sessions		Final clinical assessment	Final robotic assessment	Usability evaluation 2
Time point		Day –2	Day –1	Day –1	Day 0-6	Day 7-13	Day 13	Day 14-20	Day 21-27	Day 27	Day 27	Day 27
Time range (days)		–4 to +1	±2	±1	—^a^	—	±2	—	—	±2	±2	±2

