**Usability**												
	SUS^j^, PSSUQ^k^, TLX^l^, NPS^m^, CSAT^n^	—	—	—	—	—	SO	—	—	—	—	SO
	VAS-smiles^o^	—	—	—	SO	SO	—	SO	SO	—	—	—

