During the last session of the minimally supervised phase, a checklist (Multimedia Appendix 1) is used by the therapist to record whether participants learned how to correctly perform each assigned therapy exercise. The checklist is also used to assess the patient’s functional independence in ambulation and in positioning in front of the device and to decide if the patient meets the requirements to train with the technology in a safe and effective way without supervision. If the requirements are met, the participant can proceed to the unsupervised phase, which lasts for 2 weeks. During the unsupervised phase, patients can independently exercise with the rehabilitation platform during their free time, during dedicated sessions indicated on their therapy schedule, as well as after 5 PM and during the weekend. Specific guidelines on how much to train are not provided. Even though a possible time to train with the device is suggested on the patient’s daily therapy schedule during weekdays, patients are clearly told that they do not necessarily need to attend the session but can rather freely decide when to seek additional therapy within the offered slots or whether to go at all (ie, as a way to simulate home settings).

If, at the end of the first week of minimally supervised therapy, the patients do not meet the requirements to transition to the unsupervised phase, they continue with minimally supervised therapy for an additional week. At the end of the second minimally supervised week, the checklist is performed again. If the patients are now ready for unsupervised training, they can proceed to 1 week of unsupervised therapy; if they are not ready, they undergo a third week of minimally supervised sessions (Figure 2).

During the entire study, the device is placed in an open-access room and an emergency call system is available next to it. Trained personnel of the clinic turn on the device in the morning and turn it off in the evening. If needed, patients are taken to the device by the personnel of the clinic responsible for patient transportation. The personnel might also help patients to position themselves in the correct way in front of the device but do not help with placing the patient’s hand on the handles or operating the device.

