The usability of the platform and user experience during robot-assisted therapy is rated a first time at the end of the first week of minimally supervised therapy and a second time at the end of the study. The difference in the ratings between the 2 time points is used to investigate the effect of unsupervised training (ie, of the therapist’s absence) on the perceived usability of the therapy platform and on the user experience during technology-assisted rehabilitation.

Adverse events and device deficiencies are monitored throughout the whole study protocol. The intervention can be discontinued after consultation with medical doctors and therapists or if the participant decides to quit.

For each patient, attendance to the robot-assisted therapy sessions is registered. As attendance to robot-assisted therapy is one of the study outcomes, strategies to increase adherence are not implemented. Reasons for nonattendance are registered a posteriori for each missed supervised or minimally supervised session as well as if patients train for less than 50% of the possible days (ie, less than 7 of 14 days when the patient undergoes 2 weeks of unsupervised therapy or less than 4 of 7 days in cases where the patient undergoes only 1 week of independent training) during the unsupervised phase.

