### Outcome Measures

#### Primary Outcomes

The primary outcomes of this study are the feasibility of the proposed protocol, the dose of unsupervised robot-assisted therapy performed by participants, and the difference between usability and user experience between the phases where a therapist is present (ie, supervised and minimally supervised phases) and the unsupervised phase.

Feasibility is measured as the number of patients who could transition to the unsupervised phase out of the total number of tested patients, attendance during the unsupervised phase, and safety of use. Attendance is defined as the percentage of days out of the total number of offered days where the patient trains with the device at least once, while safety is defined as the number of adverse events and device deficiencies throughout the entire protocol.

The different metrics used to characterize therapy dose are therapy duration in minutes, number of task repetitions (ie, the number of target movements performed), and percentage change in physical therapy time with respect to the conventional therapy program. Total conventional physical therapy time is estimated from the sum of the duration in minutes of the physiotherapy (without differentiating between upper limb and lower limb) and occupational therapy sessions regularly performed by each patient at the clinic.

Platform usability is assessed with the System Usability Scale [29], the raw Task Load Index [30], and the Post-Study System Usability Questionnaire [31]. User experience during robot-assisted therapy is assessed with the Net Promoter Score [32] and the Customer Satisfaction Score, as well as by evaluating the reasons (if any) for not attending the therapy sessions with the device.

The results of the checklist used to define which patient can proceed to unsupervised therapy are also used to identify specific aspects of the platform that might need to be further improved.

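### The paired usability tests are meant to show the effect of the therapist's absence, but their population is not limited to patients who reached the unsupervised phase

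*Protocol article*

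**What the plan says.** **Purpose.** Primary Outcomes includes "the difference between usability and user experience between the phases where a therapist is present" and the unsupervised phase. The Intervention section gives the same purpose: "The difference in the ratings between the 2 time points is used to investigate the effect of unsupervised training", which it explains as the effect of the therapist not being there.

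**Data.** Evaluation 1 falls at the end of the first minimally supervised week and evaluation 2 at the end of the study. The Figure 2 legend says that at the end "the clinical and robotic assessments as well as the evaluation of the user experience and usability are repeated for all patients".

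**Pathways.** Patients who pass the checklist after week 2 have two unsupervised weeks. Those who pass after week 3 have one. For patients who fail both checks, the Intervention section says "if they are not ready, they undergo a third week of minimally supervised sessions", so they have none.

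**Tests.** Data Analysis states that for each usability metric a paired test "will be performed to compare the data collected during the usability evaluation 1 and usability evaluation 2 sessions". No population is named. The next paragraph covers intensity, performance, effective-time ratio and VAS-smiles across the three phases, and ends: "Patients who did not reach the unsupervised phase will be excluded from this analysis".

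**Status.** The text treats the usability and user experience difference as primary. Table 1 marks the same five questionnaires as secondary at both evaluations.

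**The concern.** A patient who never trains alone gives two ratings, both after weeks with a therapist in the room. The difference between them may reflect practice, fatigue or recovery, but not the therapist's absence. Pooling it with the differences from patients who did move to unsupervised use gives an average that no longer answers the stated question.

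The restriction is written where it matters least. The three-phase comparison needs a value from the unsupervised phase, and a non-transitioner has none, so that patient could not contribute a complete set anyway. In the paired usability tests a non-transitioner has both values, so only a written rule keeps that patient out. VAS-smiles and the five questionnaires share one block of Table 1, yet the exclusion is stated only for VAS-smiles.

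The Discussion hopes that usability and user experience do not drop without supervision. Non-transitioners whose ratings stay level would pull a real drop towards no change. With 13 patients, each one carries 1/13 = 7.7% of the mean.

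**Working it through.** **Inputs from the article.** N = 13 (Sample Size). Its derivation reproduces: 10/(1 − 0.20) = 12.5, rounded up to 13. Results says 13 patients completed the protocol, so I take all 13 as having both evaluations. How many transitioned is not given.

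**Assumptions, not in the article.** k = number who never transition, 0 to 5. For power only: two-sided alpha 0.05, SD of paired differences 1, true change in transitioners 0.8 SD, no mean change in non-transitioners.

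**Dilution.** Let D be the mean change in transitioners and m the mean change in non-transitioners. The all-patient mean is

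[(13 − k) × D + k × m] / 13.

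With m = 0 this is D × (13 − k)/13. Power for transitioners only comes from the noncentral t with n = 13 − k. Power for all 13 comes from 200,000 simulated trials.

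| k | Share of D kept | Power, transitioners only | Power, all 13 |
|---|---|---|---|
| 0 | 100% | 75% | 75% |
| 1 | 12/13 = 92% | 71% | 67% |
| 2 | 11/13 = 85% | 67% | 58% |
| 3 | 10/13 = 77% | 62% | 49% |
| 4 | 9/13 = 69% | 56% | 40% |
| 5 | 8/13 = 62% | 50% | 32% |

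Under these assumptions the smaller, restricted sample has more power than the full one whenever k is at least 1.

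**Other effect sizes, k = 3.** For a true drop of 1 SD, power is 80% restricted and about 66% pooled. For 0.5 SD it is 29% and 23%, weak either way.

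**Direction, with k = 3 and D = −1 SD.**
- Non-transitioners improve by 0.5 SD: (−10 + 1.5)/13 = −0.65. The drop is understated.
- Non-transitioners worsen by 1.5 SD: (−10 − 4.5)/13 = −1.12. The drop is overstated.
- The sign reverses only if 3 × m exceeds 10, so m must be over 3.3 times the true drop. For k = 1 the factor is 12/1 = 12, and for k = 4 it is 9/4 = 2.25.

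**The case against.** **Inclusion is inferred.** No sentence puts non-transitioners in the usability tests. The Figure 2 legend governs collection, and a patient without an unsupervised phase arguably has no value on the outcome as Primary Outcomes defines it. A condensed article may also leave test populations to a fuller document. This tempers the wording of the point but does not remove it. The article names the test, its data and an exclusion, and attaches that exclusion only to the following analysis. Stretching it back over the paragraph before is strained, and one sentence would settle it.

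**The size is unknown.** This stands. The article gives no k, effect size or alpha, and the sample size was justified by feasibility, not by power for this test. The number who transition is itself a feasibility outcome, so readers of the results could judge the dilution.

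**Stronger readings.** A reader might infer that the bias must favour the hoped-for result, or that it could plausibly reverse the finding. Neither is supported. Patients who fail the checklist twice may come to rate the device worse, and reversal needs the very large opposite changes shown above.

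A reader might also think that the plan's rule demands a completed unsupervised session. It does not: it excludes those who did not reach the phase. The Intervention section leaves attendance in that phase to the patient, so dropping transitioners who never trained could remove those whom the device put off.

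**Late transitioners.** Their first rating comes a week before supervision ends, so their difference spans one more supervised week. It is still a therapist-present rating followed by one after the unsupervised phase, and direct transitioners also gain practice between ratings. This is a refinement, not an error.

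**Conclusion.** The point holds as a mismatch between the stated purpose of the usability comparison and the patients whom the test, read as written, would include. If k of 13 never transition and their ratings do not change, the estimate keeps 92% (k = 1) to 69% (k = 4) of the change in transitioners. This rests on an assumed k and on no change in non-transitioners. With k = 0 the two analyses are identical, and worsening ratings in non-transitioners would push the bias the other way. The power figures are illustrative.

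The article does not show that the reported result will be biased, because it does not say how many patients failed to transition. Calling this a flaw in a primary outcome rests on the Outcome Measures text alone, since Table 1 marks the same questionnaires as secondary. In a 13-patient feasibility study that also reports these ratings descriptively, it should be fixed but is not critical.

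**What to change.** 1. In Data Analysis, state that patients who did not reach the unsupervised phase are also excluded from the paired SUS, TLX, PSSUQ, NPS and CSAT tests, and report their two sets of ratings separately and descriptively.
2. Do not add a minimum of one completed unsupervised session. Keep transitioners who chose not to train and report them as such.
3. Optionally, add a sensitivity analysis in patients who transitioned directly after the first minimally supervised week.
4. Reconcile the status of these questionnaires between Primary Outcomes and Table 1.

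The cost is a sentence or two and no new data. The paired tests lose k patients. Results describes data analysis as ongoing, so the population should be fixed before the comparison is examined. If that is no longer possible, the report should give the restricted and the all-patient results together and state k.

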## Results

Recruitment started in November 2020. As of April 2023, 13 patients were recruited and completed the protocol. Data analysis is ongoing, and publication of the results is expected for 2023.

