The absence of supervision during rehabilitation certainly raises challenges with respect to adherence and motivation to train, understanding of tasks to be achieved, and safety. We expect that an initial standardized training procedure can help patients to learn how to use a rehabilitation technology in a controlled way so that the risk of adverse events during unsupervised therapy is reduced and patients feel comfortable and motivated in using the technology on their own. Despite the many feasibility studies describing unsupervised technology-assisted rehabilitation, there exists no consensus on how to optimally achieve the transition from supervised to unsupervised use of such technologies, nor is there an agreement on how to define and evaluate feasibility. The systematic approach outlined in this protocol paper provides a way for patients to progressively transition from supervised to unsupervised use of a rehabilitation technology based on objective data (ie, a checklist). Furthermore, it allows for the collection of information on the feasibility of unsupervised therapy and its effect on therapy dose, user experience, and the usability of the rehabilitation technology used. We expect this systematic approach to allow patients to transition to unsupervised use of a rehabilitation technology in a safe and comfortable way, meaning that usability and user experience do not drop during unsupervised use. High perceived usability and user experience are essential and increasingly investigated aspects [11,24,44] as they may increase adherence, and therefore, therapy dose, in the unsupervised phase, potentially leading to an improvement in functional outcomes.

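### With at most 13 patients, a non-significant difference test is weak evidence that therapy content, VAS-smiles and usability are preserved without the therapist, yet the article names no other criterion

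*Protocol article*

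**What the plan says.** Under Data Analysis, "1-way repeated measures ANOVA or its nonparametric version (Friedman test) with post hoc tests will be run" to compare intensity, performance and the ratio of effective to total session time across the supervised, minimally supervised and unsupervised phases. VAS-smiles is handled by the same tests. The section then says "we expect therapy content and VAS-smiles not to vary significantly depending on the level of supervision", on the ground that the therapist's absence should ideally make no difference. For this comparison, "Patients who did not reach the unsupervised phase will be excluded from this analysis".

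Secondary Outcomes gives the purpose: the comparison is meant to show whether therapy content changes once the therapist has gone.

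For each usability metric, Data Analysis plans a paired t test or a paired Wilcoxon test between usability evaluations 1 and 2. That paragraph states no expected result. The expectation is in the Discussion, which hopes for a safe and comfortable transition, "meaning that usability and user experience do not drop during unsupervised use".

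Sample Size says "The study includes 13 patients; 10 patients are expected to be sufficient to perform a feasibility study", and Results says "As of April 2023, 13 patients were recruited and completed the protocol".

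**The concern.** The result the investigators hope for is that little or nothing changes. The only inferential tool named is a test designed to detect change. Such a test gives the hoped-for answer more often as the sample shrinks, whether or not anything has changed. With at most 13 patients, a real decline in content, session experience or usability could easily yield a non-significant p-value. A reader could then take that p-value as evidence of preservation, because the expectation is itself worded in terms of significance. What is at stake is how the finished study describes therapy without a therapist: as shown to be similar, or as not shown to differ.

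**Working it through.** **Inputs from the article**
- Enrolled: 13. Judged sufficient: 10. Allowed dropout: about 20% (Sample Size).
- Recruited and completed: 13 (Results). The number who reached the unsupervised phase is not given, so the content and VAS-smiles comparisons have at most 13 patients.

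**Assumptions (not stated in the article)**
- Two-sided 5% level.
- Effects are in SDs of the within-patient difference, because no SD or within-patient correlation is given.
- Range shown: n = 10 (the article's own sufficient number) to n = 13 (the maximum).

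**1. The article's own figure.** 10 / (1 − 0.20) = 12.5, rounded up to 13. It reproduces. The 10 is a feasibility judgement with no power calculation behind it.

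**2. Power for a moderate change.** For a paired t test, power comes from the noncentral t distribution with n − 1 degrees of freedom and noncentrality d·√n. With d = 0.5:
- n = 10: noncentrality 0.5 × √10 = 1.58, power 29%.
- n = 13: noncentrality 0.5 × √13 = 1.80, power 38%.

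A true change of 0.5 SD would therefore give a non-significant result in 71% (100 − 29) or 62% (100 − 38) of such studies.

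**3. Change detectable with 80% power.**

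| Test | n = 10 | n = 13 |
|---|---|---|
| Paired t, 5% | 1.00 SD | 0.85 SD |
| Three-phase repeated-measures ANOVA (sphericity, only the unsupervised phase shifted) | 0.93 SD | 0.80 SD |
| Post hoc pair, Bonferroni over 3 | 1.22 SD | 1.02 SD |

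The planned three-phase test is thus little better than the paired test, and corrected post hoc tests are worse.

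**4. What a non-significant result leaves open.** The 95% CI half-width is t(0.975, n − 1) / √n:
- n = 10: 2.262 / 3.162 = 0.72 SD.
- n = 13: 2.179 / 3.606 = 0.60 SD.

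A result is just non-significant when the observed difference about equals the half-width. The interval then runs from about zero to twice the half-width: 1.43 SD (n = 10) or 1.21 SD (n = 13). If the observed difference were exactly zero, the interval would exclude changes beyond 0.72 or 0.60 SD.

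**5. Sensitivity to the unit.** In between-patient SDs, multiply by √(2(1 − ρ)), where ρ is the within-patient correlation. At n = 13 the half-width is 0.86 (ρ = 0), 0.60 (ρ = 0.5) or 0.38 (ρ = 0.8). The change detectable with 80% power is 1.20, 0.85 or 0.54.

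**6. What a margin would deliver.** Take an illustrative largest acceptable drop of 0.5 SD and a true change of zero. The chance that the 95% interval excludes that drop depends on the same noncentrality as in step 2, so it is 29% (n = 10) to 38% (n = 13). A two-sided equivalence test (two one-sided tests at 5%) with the same margin succeeds in about 7% (n = 10) to 13% (n = 13); about 36 patients would be needed for 80%.

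**The case against.** The strongest reply is that the article states an expectation and no decision rule. A reader might infer that the plan treats p>0.05 as proof of no impact, but no sentence says so. This stands, and the point is worded accordingly.

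The reply on scope also stands. The sentence about not varying significantly covers content and VAS-smiles only. Usability enters through the Discussion, where no test is attached to the hope, and the Intervention section says only that the rating difference is used to investigate the effect of the therapist's absence.

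A reader might infer that a null result here would carry the approach into the home. The article does not support that: the Discussion makes the home step conditional on feasibility, which Primary Outcomes measures by transition, attendance and safety. The content comparisons are secondary outcomes. The usability difference is listed as primary in the text, although Table 1 marks the questionnaires as secondary.

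A reader might also infer that the tests cannot exclude a change of nearly 1 SD. That confuses the change detectable with 80% power with the bound the data set, which depends on the estimate (step 4).

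Finally, intervals, alpha and margins are often left to a full protocol or SAP, and descriptive statistics are planned for usability and user experience. That is fair, and their absence is not the complaint. The complaint is that the stated expectation is put in terms of significance, and neither the full protocol nor descriptive summaries alter that wording.

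**Conclusion.** The point holds as a matter of interpretation. The article seeks reassurance that content, VAS-smiles and usability are preserved, and it relies on difference tests in 13 patients or fewer with no other criterion for preservation. At an assumed two-sided 5% level, non-significance would be the likely result even if there were a true change of 0.5 SD of the within-patient difference (62% to 71% of studies for 13 to 10 patients), and a just non-significant result would be compatible with about 1.2 to 1.4 SD. These are paired-t figures. The size in raw units depends on an unstated correlation, and fewer than 10 evaluable patients would make matters worse. None of this shows the sample of 13 to be wrong for a feasibility study, and it does not bear on the feasibility criteria.

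**What to change.** For each content, VAS-smiles and usability metric, report the paired difference (unsupervised minus minimally supervised; for usability, evaluation 2 minus evaluation 1) with its 95% CI. Use a Hodges-Lehmann or bootstrap interval where the data are skewed. Replace the expectation of non-significance with interpretation of that interval, and state that a non-significant test will not be read as no change. If a largest acceptable drop is used for any metric, fix it before the results are seen. Results says that all 13 patients have completed and analysis is under way, so a margin set after results are known must be labelled post hoc.

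The cost is a few sentences of analysis wording and one interval per metric, with no new data. The downside is that most metrics will probably be reported as inconclusive: with an illustrative 0.5 SD margin and no true change, the 95% interval would exclude the drop in only 29% to 38% of cases.
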